### Screening visit

After obtaining informed consent, a screening visit will take place at the outpatient clinic. The study physician checks in- and exclusion criteria and performs a physical examination. Laboratory tests are taken (haematology, coagulation profile and electrolytes, see Table 2). If not already done so, baseline MRI and CT of the liver as well as HIDA scans are performed and assessed for mRECIST criteria and baseline FLR function respectively [26]. All patients are asked to fill out quality of live questionnaires at this and subsequent visits.

**Table 2 Tab2:** Laboratory examination

Category	Parameter
Haematology	Leukocytes, erythrocytes, haemoglobin (Hb), haematocrit (HCT), mean corpuscular volume (MCV), mean corpuscular haemoglobin (MCH), mean corpuscular haemoglobin concentration (MCHC), and platelet count
Coagulation profile	INR, PT, APTT
Serum chemistry	Sodium, potassium, phosphate, creatinine, total bilirubin, alkaline phosphatase, SGPT/ALT, SGOT/AST, GGT, glucose, albumin, CRP, LDH, alpha-fetoprotein

Total: max 10 ml

### Scout and treatment procedures

Patients who fulfill the selection criteria at the screening visit will first receive a preparatory angiography and scout dose within four weeks. During angiography, the hepatic arterial vasculature is carefully assessed with digital subtraction angiography and C-arm CT. One or multiple injection positions are chosen that will cover the intended liver volume whilst minimizing the chance of activity deposition in non-target organs (e.g., intestines, pancreas). In the unlikely event that a vessel poses a threat to possible extrahepatic deposition of microspheres, it will be coil-embolized.

Then, a scout dose of ^166^Ho-microspheres (i.e,. approximately three million microspheres; 250 MBq) will be administered during the same procedure [30]. Because the gamma-radiation of ^166^Ho is visible even at such low activities, ^166^Ho-scout can be used to predict the intrahepatic distribution of a therapeutic dose of ^166^Ho-microspheres. It can thus be used to estimate the activity needed during the actual treatment to obtain the necessary dose for the specific dose cohort the patient is in (i.e. treated non-tumorous liver-absorbed dose).

After administration of the scout dose, the patient will be transferred to the SPECT/CT and will be subjected to scintigraphy to assess intrahepatic and extrahepatic activity. Both planar imaging of the thorax and abdomen will be performed, as well as SPECT/CT of the abdomen. Images will be evaluated qualitatively and quantitatively. The angiography, scout dose administration and SPECT/CT are performed during a one-day visit.

The following formulas are used to calculate the activity needed during the actual treatment [33]:$$A={D}_{NTT}*\frac{(TNR*{M}_{T})+{M}_{NTT}}{15.9*\left(1-LSF\right)}$$where $$A$$ is the activity in GBq; $${D}_{NTT}$$ the desired dose to the ipsilateral non-tumourous liver tissue ($$NTT$$) (i.e., 50 Gy, 60 Gy, etc.); $$TNR$$ the tumour-to-non tumour liver tissue ratio; $${M}_{T}$$ and $${M}_{NTT}$$ the mass of the tumour ($$T$$) and ipsilateral non-tumourous liver tissue ($$NTT$$) in kg; and $$LSF$$ the lung shunt fraction. The lung shunt fraction is calculated as:$$LSF=\frac{{C}_{lungs}}{{C}_{lungs}+{C}_{liver}}$$where $$C$$ indicates the total counts calculated on post-scout SPECT/CT in the lungs and the perfused liver.

Lastly, the tumour-to-non tumour liver tissue liver tissue ratio ($$TNR$$) can be inferred from the scout distribution using:$$TNR=\frac{{A}_{T}*{M}_{T}^{-1}}{{A}_{NTT}*{M}_{NTT}^{-1}}$$where $${A}_{T}$$ and $${A}_{NTT}$$ is the total activity to the tumour ($$T$$) and non-tumourous tissue ($$NTT$$) measured on the post-scout SPECT/CT.

Besides predicting the distribution within the perfuse lobe, the scout dose serves to exclude any extrahepatic deposition during the actual treatment. It is as such a safety procedure. Notably, estimated lung shunting of more than 30 Gy based on the post-scout SPECT/CT is a contraindication for treatment dose. Activity in the falciform ligament, portal lymph nodes and gallbladder is accepted.

If the scout dose does not reveal any contraindications, patients will undergo ^166^Ho unilobar radioembolization treatment within 2 weeks. Treatment will be performed in a similar fashion as the preparatory angiography, with identical injection positions. SPECT/CT will follow in a separate visit three-to-four days after the intervention to quantify dosimetry.

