**Fig. 2 Fig2:**
[figure not shown]
Study flowchart. Eligibility is assessed during the screening visit (patient and tumor characteristics) as well as the scout dose (lung shunting, extrahepatic depositions, etc.). Patients will be considered included once they received the actual treatment dose. The post-treatment follow-up visits serve to map toxicities, as well as to evaluate eligibility for resection. *The exact interval will be at 1.5, 3, 4.5, 6 and 9 months. The last follow-up will be at 9 months following treatment (if not converted) or 3 months after hepatectomy

**Table 1 Tab1:** Study procedures

Procedures	Screen	Scout	Treatment	SPECT/CT	Follow-up^a^	S	Post-S visit^b^
Informed consent	E						
In-/exclusion	E	E					
Demographic data	X						
Physical exam, vital signs and clinical performance status (ECOG)	X	E	X		X	X	X
EORTC QLQ C30, HCC 18, BPI-SF	E	E	E		E	E	E
MRI / CT liver	X				X^c^	X^c^	X^c^
CT thorax	X						
HBS	X				X		
Angiography		E	E^d^				
Scout dose		E					
Therapeutic dose			E				
SPECT/CT + contrast CT		E		E^e^			
Laboratory examination	X	E	X		X	X	X
Monitoring of (S)AE’s + concomitant med		E	X		X	X	X
Pregnancy test		X					

E = extra activity in study context, X = standard care, W = week, M = month, S = Surgery

^a^Exact interval is at 1.5, 3, 4.5, 6 and 9 months. However, post-radioembolization follow up will be discontinued as soon as patients are eligible to undergo surgical resection. ^b^Three months following surgery. ^c^MRI is standard. CT is performed if MRI is contraindicated. ^d^Venogram when standard therapy (PVE) is performed. ^e^Three to four days after the therapeutic treatment, at separate visit in outpatient clinic

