#### Sample size

This study is designed with four dose cohorts, starting at 50 Gy and going up to 80 Gy. The last cohort will consist of at least six patients. This means that the maximum number of patients (i.e., if in each cohort one dose-limiting toxicity occurs, see Design for details) will be (3 + 3) × 4 = 24 patients. The minimum number of patients will be two, which is when two patients in the first (50 Gy) cohort experience a dose-limiting toxicity. If during the entire study no patient experiences a dose-limiting toxicity, the number of patients will be 3 × 4 + 3 = 15.

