## Discussion

HCC requires a multidisciplinary approach involving specialists in hepatology, oncology, interventional radiology, nuclear medicine, pathology and surgery. The RALLY study aims to assess the safety of unilobar ^166^Ho unilobar radioembolization as a means of converting patients with insufficient FLR to resectability.

To date, numerous studies investigated the outcomes of unilobar radioembolization [11–20]. Albeit retrospectively, these studies reveal the safety and efficacy of unilobar radioembolization in achieving ipsilateral tumour control and contralateral hypertrophy and indicate that surgical resection of radiated liver lobes is safe and technically feasible. Sufficient FLR response can be expected three to five months following unilobar radioembolization. Virtually all studies base FLR sufficiency on its volume relative to total liver volume. However, assessing FLR function may better predict the risk of post-hepatectomy liver failure [34]. We recently reported favorable surgical outcomes in a set of patients where HIDA scan was routinely used to assess FLR sufficiency [19]. The RALLY study will therefore determine the sufficiency of the FLR with a HIDA scan, using a cutoff of 2.7%/min/m^2^ [32].

Current activity planning methods are either based on the body surface area (BSA) model or the Medical Internal Radiation Dose (MIRD) mono-compartment model (Fig. 3 left panel) [33, 35]. In the BSA model, the prescribed activity is calculated using the total body surface area and the fractional liver involvement. In the MIRD mono-compartment model, the activity is based solely on the target liver mass. Both methods assume a homogeneous distribution of microspheres between tumourous and non-tumourous liver tissue and thus ignore the actual spatial microsphere distribution. This may lead to over- or under dosing [35–37]. A scientifically more sound method is the so-called multi-compartment model (Fig. 3 right panel). This model factors in the microsphere distribution between three compartments -i.e., tumour-, non-tumourous liver- and lung tissue- by obtaining activity output from post-scout SPECT/CT and planar scintigraphy images. This personalized model more accurately predicts absorbed doses [38].

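### The lung shunt fraction and the 30 Gy lung check rely on a SPECT/CT described as abdominal; the sections must agree on one source of lung counts

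*Protocol article*

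**What the plan says.** The statements on scout imaging are in two parts of the protocol article.

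- **Field of view** (Scout and treatment procedures): "Both planar imaging of the thorax and abdomen will be performed, as well as SPECT/CT of the abdomen". The thorax is assigned to planar imaging and the abdomen to SPECT/CT.
- **LSF definition** (same section): LSF = C_lungs / (C_lungs + C_liver), where C "indicates the total counts calculated on post-scout SPECT/CT in the lungs and the perfused liver".
- **Lung contraindication** (same section): "estimated lung shunting of more than 30 Gy based on the post-scout SPECT/CT is a contraindication for treatment dose".
- **Dose model** (Discussion): the model with tumour, non-tumourous liver and lung compartments is fed "by obtaining activity output from post-scout SPECT/CT and planar scintigraphy images".

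Table 1 lists "SPECT/CT + contrast CT" at the scout visit and gives no field. The only thoracic scan it lists is a CT at screening, which yields no activity counts.

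**The concern.** An abdominal field holds at most the lower part of the lungs, so it cannot supply a total lung count. Read literally, the LSF definition asks for a quantity that the described acquisition does not contain. The Discussion names a second source, which leaves the reader with two descriptions of where lung counts come from.

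One LSF serves two purposes. It determines whether a patient may receive the treatment dose at all, and it scales the therapeutic activity through 1/(1 - LSF). The cohorts are defined by projected dose to non-tumourous liver ("This study is designed with four dose cohorts, starting at 50 Gy and going up to 80 Gy"), so an error in LSF also moves the delivered dose away from the cohort label. The trial runs at four centres in two countries with three to six patients per cohort. Conflicting text could let centres derive LSF differently within one cohort.

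**Working it through.** The documents give no LSF, lung mass, lung dose or share of lung in the field, so there is no stated figure to reproduce. The check applies the protocol's own formulas to a partial lung field.

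**Inputs**

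- From Scout and treatment procedures: the LSF formula, and A = D × S / (15.9 × (1 - LSF)), where S = TNR × M_T + M_NTT.
- From Sample size: target doses D of 50 to 80 Gy.
- Assumed: true LSF L of 3%, 10% or 20%; share c of lung counts in the field of 0.2 to 0.5.
- Assumed for the lung check only: lung dose = 15.9 × A × LSF / M_lung, M_lung of 0.8 to 1.2 kg, S of 1.0 to 2.0 kg.

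**Step 1: estimated LSF.** LSF_est = cL / (cL + 1 - L). At L = 10%:
- c = 0.2: 0.02/0.92 = 2.2%
- c = 0.5: 0.05/0.95 = 5.3%

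**Step 2: activity.** A_est / A_true = (1 - L)/(1 - LSF_est), which simplifies to 1 - (1 - c)L. The shortfall is therefore (1 - c)L.

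| True LSF | Shortfall, c = 0.5 | Shortfall, c = 0.2 | Delivered at an 80 Gy target |
|---|---|---|---|
| 3% | 1.5% | 2.4% | 78.8 to 78.1 Gy |
| 10% | 5% | 8% | 76.0 to 73.6 Gy |
| 20% | 10% | 16% | 72.0 to 67.2 Gy |

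Up to an LSF of 10% the loss is at most 6.4 Gy, less than the 10 Gy step between cohorts. At 20% it is 8.0 to 12.8 Gy, about one step.

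**Step 3: lung dose reading.** For the activity actually given, estimated/true lung dose = LSF_est / L = c / (1 - (1 - c)L).
- L = 10%: 0.2/0.92 = 0.217 to 0.5/0.95 = 0.526, so a true 30 Gy reads as about 6.5 to 15.8 Gy.
- L = 20%: 0.2/0.84 = 0.238 to 0.5/0.90 = 0.556, so a true 30 Gy reads as about 7.1 to 16.7 Gy.

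**Step 4: where the check trips.** Let o = 30 × M_lung / (D × S). Over the assumed masses and D of 50 to 80 Gy, o runs from 30 × 0.8/(80 × 2.0) = 0.15 to 30 × 1.2/(50 × 1.0) = 0.72.
- With full lung coverage the check trips at LSF = o/(1 + o), which is 13.0% to 41.9%.
- With partial coverage it trips at a true LSF of o/(o + c): 23.1% to 59.0% at c = 0.5, and 42.9% to 78.3% at c = 0.2.
- The true lung dose at a reading of 30 Gy is 30 × (1 + o)/(c + o): about 42 to 53 Gy at c = 0.5, and 56 to 99 Gy at c = 0.2.

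**Sensitivity.** At c = 0.75 the activity shortfall at L = 10% is 2.5%, and a reading of 30 Gy corresponds to about 35 to 38 Gy. At c = 1 both errors vanish.

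**The case against.** A reader might infer that lung counts in this trial are in fact truncated and that patients are being under-screened. The documents do not support that. The sentence that limits SPECT/CT to the abdomen also provides planar views of the thorax, and the Discussion names planar images as a model input. The Background presents SPECT/CT as improving the estimation of lung shunting, so the reference to the abdomen may be loose shorthand for a wider field. The article condenses a fuller protocol, where bed range and counting procedure would normally be set out. This objection stands against any claim of demonstrated bias. It does not remove the conflict, because the article itself prints the field, the count source and the check, and they do not agree.

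A second tempting inference is that the maximum tolerated dose would be materially wrong. This too goes beyond the documents. The dose effect is a small under-delivery at low shunt, and a SPECT/CT three to four days after treatment is planned to quantify dosimetry, so a shortfall could be seen. That scan comes too late to serve the pre-treatment lung exclusion.

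The sizes also rest on an in-field share that appears nowhere in the documents. That is correct, which is why they are given as ranges. The direction of the error does not depend on the share, provided it is below 1.

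**Conclusion.** The point holds as an inconsistency in a stated calculation rule, with conditional consequences. If the abdominal SPECT/CT supplies the lung counts as written, LSF is too low and two errors follow. They differ in kind and size.

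- **Lung check (the main concern).** The estimate is too low, so the exclusion errs in the unsafe direction. With 20% to 50% of lung counts in the field, the reading is roughly a fifth to a half of the true lung dose. The effect matters only for patients with a high shunt, and the documents do not say how common they are.
- **Activity.** It is too low by (1 - c)L: 1.5% to 2.4% at a true LSF of 3%, and 5% to 8% at 10%. This is under-delivery against the cohort label.

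Both sizes depend on the assumed in-field share, and the figures for where the lung check trips depend also on assumed masses. Whether any truncation occurs in practice cannot be settled from the article.

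**What to change.** Reconcile the imaging sentence, the LSF definition and the lung contraindication in Scout and treatment procedures with the model description in the Discussion. State one acquisition whose field covers the whole lungs as the source of both C_lungs and C_liver. This could be the planar thorax and abdomen views already acquired, or a SPECT/CT field stated to include the thorax. Use the resulting LSF in both the activity formula and the existing lung-dose check, in the same way at every centre.

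The cost is a wording change if the planar images are named, or a longer bed range in the same session if SPECT/CT is named. The 30 Gy threshold and the cohort doses are left as they are.

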### Post-treatment follow-up

After treatment, patients will be tentatively scheduled for follow-up visits after 1.5, 3, 4.5, 6 and 9 months. The main goal of these follow-up visits is to evaluate the eligibility of the patient to proceed to surgical resection and to map the toxicity and response following ^166^Ho-radioembolization. The study participation for a patient will end if the patient is unable to undergo surgical resection within 9 months. During each visit, laboratory (Table 2) and clinical toxicities will be monitored. Tumour response is assessed using MRI (or CT if contra-indicated) with mRECIST [26]. FLR response is assessed using HIDA and MRI.

### Hepatectomy and post-surgery follow-up

If tumour burden, performance status and FLR (> 2.7%/min/m^2^) allows for resection, the patient will be operated on as soon as possible. Eligibility for resection will be discussed in a multidisciplinary tumour board. The patient undergoes general anesthesia and the abdomen will be explored to rule out extrahepatic disease. The extent of the hepatectomy will be determined intraoperatively with the aim of achieving R0 resection. Directly following resection, surgical specimens of both tumour- and non-tumour tissue will be processed for routine histological evaluation as well as inclusion in the RALLY biobank (see heading ‘Biobank’). After resection, patients will receive a last follow-up visit three months after resection during which toxicities, surgical complications (using Clavien-Dindo) and tumour burden will be assessed [27].

### Biobank

Resection specimens will be fresh-frozen and formalin-fixed paraffin embedded for future molecular analyses. A blood sample (20 mL maximum) will be drawn from the venous line during the surgical procedure. This will be used as a genome reference. The processed body material is stored in the designated RALLY biobank under the management of the UMC Utrecht (in -80° C freezers or in nitrogen vessels for fresh frozen material). For participating sites, the material is first temporarily stored according to the guidelines of the respective center’s biobank. Afterwards, the specimens will be transported to the UMC Utrecht and stored in the RALLY biobank.

### Statistics and data management

#### Statistical analysis

Descriptive statistics (n, mean, standard deviation, 95-CI, median, minimum and maximum) will be calculated for each quantitative variable; frequency counts by category will be made for each qualitative variable. Two sets of study data will be evaluated: the primary endpoint will be evaluated in the Full Analysis Set. The Full Analysis Set is defined as the set of data generated from the included patients who received at least the treatment dose. The secondary endpoints will be evaluated in both Full Analysis Set and Per Protocol Set. The Per Protocol Set is defined as the set of data generated from the included patients who complied with the protocol. A linear mixed effects regression model will be used to evaluate the relationship between absorbed dose- and studied effect. An analysis of variance method with a Chi-square test will be used to compare nested models and generate p-values for the fixed effects. The explained variance by the model, with and without random intercept, will be assessed with R^2^ for mixed effects models.

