## Methods/design

### Aims and outcomes

The primary objective of this study is to establish the maximum tolerated non-tumourous liver-absorbed dose of ^166^Ho microspheres in patients with HCC who receive unilobar radioembolization as a bridge to resection. The maximum tolerated dose is assessed in terms of the rate of unacceptable dose-limiting toxicities (see paragraph on Design). All grade 3 or higher toxicities (according to the CTCAE version 5.0 criteria) that are possibly, probably or definitively related to unilobar radioembolization are considered a dose-limiting toxicity. Exceptions to this are expected adverse events: grade 3 or higher lymphopenia and liver enzymes (AST/SGOT, ALT/SGPT, GGT, ALP), as well as post-embolization syndrome. Toxicities after unilobar radioembolization will be recorded at 6 weeks, 3, 4.5, 6 and 9 months, or up to three months after surgery. Administration technique related adverse events will not be regarded as dose-limiting toxicity.

Secondary aims include establishing a dose–response relationship between (i) the perfused/treated normal liver-absorbed dose and the FLR response and (ii) the tumour-absorbed dose and the tumour response, to map the safety and feasibility of surgical resection of converted patients, and to assess quality of life during the study procedures. FLR response will be quantified using MRI (volume of the FLR) and hepatobiliary iminodiacetic acid (HIDA) scan (function of the FLR). Tumour response will be assessed using the mRECIST criteria [26]. Dose–response relationships will be measured at baseline and at every post-unilobar radioembolization follow-up. The safety and feasibility of surgical resection will be monitored through the Clavien-Dindo grading system during the post-operative stay and at the follow-up visit three months after surgery [27]. Quality of life of patients will be assessed at every visit through questionnaires in the patient’s native language. EORTC QLQ C30, EORTC QLQ HCC and BPI-SF questionnaires and manual will be used for assessment and analysis respectively [28–30].

As a last secondary aim, a biobank will be generated of resected liver specimens and blood samples for future analyses of therapy surviving cancer cells.

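### Fixed-effect p-values for the secondary dose-response models come from a large-sample chi-square test in a trial of at most 24 patients; for a patient-level dose slope they are modestly too small

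*Protocol article*

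**What the plan says.** The Aims and outcomes section makes dose-response a secondary aim: "Secondary aims include establishing a dose–response relationship between (i) the perfused/treated normal liver-absorbed dose and the FLR response". A second relation, between tumour-absorbed dose and tumour response, follows in the same sentence. Outcomes are measured at baseline and at each follow-up visit, of which there are up to five.

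The Statistical analysis section fixes three things:
- The model: "A linear mixed effects regression model will be used to evaluate the relationship between absorbed dose- and studied effect".
- The test: "An analysis of variance method with a Chi-square test will be used to compare nested models and generate p-values for the fixed effects".
- The summary of fit: "The explained variance by the model, with and without random intercept, will be assessed with R^2^ for mixed effects models". This shows that a random intercept is intended. The grouping unit is not named.

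The section names no small-sample reference distribution, no significance level and no interval method for the slopes.

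The Sample size section gives three totals. The maximum "will be (3 + 3) × 4 = 24 patients". Without toxicity: "If during the entire study no patient experiences a dose-limiting toxicity, the number of patients will be 3 × 4 + 3 = 15". At the other end: "The minimum number of patients will be two, which is when two patients in the first (50 Gy) cohort experience a dose-limiting toxicity".

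**The concern.** Comparing nested mixed models with a chi-square test is a likelihood-ratio test. Its chi-square reference is accurate when there are many independent units. Each patient has one treatment to one lobe, so the treated normal-liver dose is the same at all of that patient's visits. For the slope on that dose, the independent units are patients, and two or three dozen scans from 15 patients still leave about 13 degrees of freedom. The chi-square reference behaves as if the residual variance were known and as if the degrees of freedom were unlimited, so the p-values come out too small.

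What is at stake is how firmly a dose-response relation for remnant growth or function can be stated. The same test would serve several outcomes (remnant volume, remnant function, tumour response) in two analysis sets, so the same bias would recur in each.

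**Working it through.** **Inputs from the protocol article.** Maximum (3 + 3) × 4 = 24 patients; no toxicity 3 × 4 + 3 = 15; minimum 2. All three reproduce from the escalation rule. The worked example under Fig. 1 uses 18.

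**Inputs assumed.** Two-sided level 5%; maximum-likelihood fit; patient as random intercept; normal errors.

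**Step 1: exact size for one patient-level slope.** With equal visits per patient, the test reduces to a regression on the N patient means. The likelihood-ratio statistic is LR = N × ln(1 + t²/(N − 2)), where t has N − 2 degrees of freedom if there is no dose effect. The plan rejects when LR exceeds 3.8415, the 95% point of chi-square on 1 df. That is the same as t² > (N − 2) × (exp(3.8415/N) − 1).

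| N | (N − 2) × (exp(3.8415/N) − 1) | critical t used | correct critical t | real size |
|---|---|---|---|---|
| 24 | 22 × 0.1736 = 3.819 | 1.954 | 2.074 | 6.4% |
| 18 | 16 × 0.2379 = 3.806 | 1.951 | 2.120 | 6.9% |
| 15 | 13 × 0.2919 = 3.794 | 1.948 | 2.160 | 7.3% |
| 12 | 10 × 0.3773 = 3.773 | 1.942 | 2.228 | 8.1% |
| 9 | 7 × 0.5324 = 3.727 | 1.931 | 2.365 | 9.5% |
| 6 | 4 × 0.8969 = 3.588 | 1.894 | 2.776 | 13.1% |

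Rows below 15 stand for early stopping. The excess over 5% is 1.4 points at 24 patients (6.35 − 5), 2.3 at 15 (7.33 − 5) and 3.1 at 12 (8.08 − 5).

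**Step 2: unequal visits.** Follow-up ends once a patient can go to surgery, so visit counts will differ. Simulation with no dose effect, 2 to 5 visits per patient and intraclass correlation 0.3, 0.5 and 0.8 (4,000 runs each) gave 6.9% to 7.2% at 15 patients and 6.4% to 6.6% at 24. This agrees with Step 1.

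**Step 3: other dose terms the model could carry.**
- Dose-by-time, random intercept only, intraclass correlation 0.3 and 0.6 (2,500 runs, standard error about 0.4 points): 6.5% and 5.8% at 15 patients; 4.9% and 5.4% at 24.
- Dose varying partly or wholly within patient, as with two or three tumours each (6,000 runs): 5.7% to 6.6% at 15 patients; 5.5% to 6.0% at 24.
- Dose cohort as a four-level factor (3 df, exact): 11.3% at 15 patients; 8.3% at 24.
- One further patient-level covariate beside the dose slope (exact): 8.6% at 15 patients; 7.0% at 24. Two further: 10.1% and 7.7%.

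The article names neither a cohort factor nor further covariates, so the last two lines show sensitivity only.

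**Step 4: does the remedy work?** Using t on N − 2 degrees of freedom, which is what a Kenward-Roger or Satterthwaite correction gives in the balanced patient-level case, the exact size is 5.0%. Simulation (20,000 runs) gave 4.96% at 15 patients and 4.85% at 24.

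**The case against.** The strongest reply has four parts.

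**Importance.** The primary objective is settled by counting dose-limiting toxicities under the 3 + 3 rule. No dose decision, stopping rule or sample size depends on a dose-response p-value. This stands, and it limits the weight of the point.

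**Size.** The article sets no significance level and no decision rule for dose-response, so 5% is an assumption made here. For a single slope the excess is only 1.4 to 2.3 points at 24 to 15 patients. That also stands.

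**Scope.** Because outcomes are measured at baseline as well as afterwards, a natural dose effect on remnant change is dose-by-time, which draws on within-patient information. There, and for tumour-level dose, the test runs at roughly 5% to 6.5%. This stands for those terms but leaves the patient-level slope untouched.

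**Condensed article.** Degrees-of-freedom methods are usually left to an analysis plan, and one that is not shown might add a correction. This does not dispose of the point. The article does not leave the test open; it names the uncorrected one and says what it is for.

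A reader might go further and infer that every dose-response claim will exceed a planned 5% error rate, that the real error is 8% to 12%, or that the confidence intervals for the slopes will be too narrow. The article supports none of these. It plans no 5% level. At 15 to 24 patients, rates of 8% or more need covariates or a cohort factor that it does not name; a single slope gets there only if the trial stops early. The only interval it mentions is among the descriptive statistics. Nor is 15 to 24 the planned range: the stated range is 2 to 24, and 15 is the case without toxicity.

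**Conclusion.** The point holds in a limited form. The stated test is anti-conservative for the slope on treated normal-liver dose, with a real size of about 6.4% at 24 patients, 7.3% at 15 and 8.1% at 12 against an assumed two-sided 5%. These figures rest on a maximum-likelihood fit, a patient random intercept and normal errors; across the intraclass correlations tried they barely move. The bias is smaller for dose-by-time and tumour-level dose. It grows if the trial stops early or if patient-level terms are added. This is a worthwhile, inexpensive improvement to a secondary analysis. It does not threaten the trial's main conclusion.

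**What to change.** Replace the chi-square sentence in the Statistical analysis section with one such as: *Fixed effects will be tested in models fitted by REML, using F-tests with Kenward-Roger (or Satterthwaite) degrees of freedom, and each dose slope will be reported with the matching 95% confidence interval.* A parametric bootstrap likelihood-ratio test is an acceptable alternative if the comparison of nested models is to be kept.

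The R² summary can stay as it is. The cost is one sentence and standard software, with no change to design, data collection or patients. The downside is slightly larger p-values: at 15 patients, a slope that the present test reports as p = 0.032 would become p = 0.05 (put t = 2.160 into N × ln(1 + t²/(N − 2)) and read the result against chi-square on 1 df).
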